#### Plan to promote participant retention and complete {18b}

In our current practice, we have noticed that very few patients refuse to attend the visit at 6 months that corresponds to the visit of the main objective (Fig. 1). A letter to remind them of the follow-up visit is sent 2 months before it. However, in case of no show or of serious adverse event (SAE; endophthalmitis, including retinal detachment), missing values for the primary endpoint will be dealt with multiple imputation*.* For the secondary endpoints, there will be no attribution of missing data.

#### Data management {19}

For each patient, a case report form (CRF) is created, which includes the data necessary to ensure compliance with the protocol and all data necessary for the statistical analysis and identify major protocol deviations. Data collection is done directly by the investigator or clinical research associate (CRA) in charge of the study, using an electronic CRF (eCRF) developed by the Promotion Department of the University Hospital of Nantes with ENNOV Clinical. The data are encoded to keep the identities of the patients confidential.

The collection of clinical data will be based on the establishment of a clinical database and the creation of input screens for image capture. The surgery videos are transferred anonymously on USB keys provided by the sponsor. A surgeon at the Department of Ophthalmology will note the gripping areas of the ERM in parallel with what the investigator has already noted.

#### Confidentiality {27}

Data collected during the study will be processed electronically in compliance with the requirements of the CNIL (compliance with the French Reference Methodology MR001). The CNIL is an independent French administrative regulatory body whose mission is to ensure that data privacy law is applied to the collection, storage, and use of personal data.

#### Plans for collection, laboratory evaluation, and storage of biological specimens for genetic or molecular analysis in this trial/future use {33}

Not applicable as no biological specimens were collected as part of this trial.

### Statistical methods

#### Statistical methods for primary and secondary outcomes {20a}

The variables measured at baseline are described for all patients in both group by numbers and percentages for each category for categorical variables and the minimum, maximum, average, standard deviation, and quartiles for the quantitative variables.

The primary endpoint is the difference between the number of microscotomas measured before surgery and the number of microscotomas measured at 6 months (a number in the range of 0–29). The mean difference is calculated in each of the two groups and compared using a mixed linear regression model to take into account the stratification of the randomization of the center (the center will be considered as a random effect) and adjustment for the preoperative number of microscotomas. Then, center-effect is analyzed with a fixed-effect model.

The following secondary endpoints are analyzed using a mixed linear regression model: comparison of the number of microscotomas in the two groups between preoperative visit and at 12 months; description and comparison of the type of microscotomas before surgery and at 1, 6, and 12 months; comparison of changes in mean visual acuity and in mean retinal sensitivity; study of the association between the presence of SANFL or DONFL with the number of microscotomas; comparison of the OCT B scan; and study of the associations between data in the OCT B scan and VA and between data in the OCT B scan and the presence of microscotomas.

The comparison between the two groups in the frequency of symptoms (blurred vision, metamorphopsia, relative scotoma, diplopia and micropsia), the comparison of the percentage of abnormalities detectable by OCT in front of the layer of optical fibers, and the comparison of the percentage of recurrence of the ERM at 12 months between the two groups are analyzed by Chi-square tests stratified on the center.

The correlation between VA and retinal sensitivity (the central point and the average of the five most central points) are analyzed according to the measurement of Pearson or Spearman’s correlation coefficients.

In addition, a description for each group of the number of microscotomas that are not located in a gripping area of the ERM and the ILM (at 1 month and 6 months) and a description of the outcome (disappearance/persistence) of microscotomas that existed before the surgery at 1 and 6 months is done.

The level of statistical significance is set at 0.05. Statistical analysis will be conducted in SAS software.

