### Eligibility criteria {10}

The patients experiencing ERM are usually aged > 60 years. The etiology is mostly idiopathic but can be secondary to various diseases (diabetic retinopathy, inflammation [uveitis], trauma, recent eye surgery, retinal detachment or tear). Idiopathic ERM affect about 7% of patients after the age of 50 years according to the Blue Mountains Eye Study (conducted on an Australian population) [24]. They are often asymptomatic and not treated. In this study, 28% of patients had a loss of VA and 7.1% had metamorphopsia (distortion of lines) [24]. They then needed surgery.

The study population concerns only patients with symptomatic idiopathic ERM, responsible for symptoms such as decreased VA and metamorphopsia.

Other inclusion criteria are patients aged ≥ 18 years and women without childbearing potential or with active contraception (intrauterine device, contraceptive pill, or contraceptive implant). For patients with both eyes affected, the treated eye in the protocol is the one that is the most severely affected.

For the patients with preoperative lens opalescence, a cataract surgery is performed. As ERM mainly affects patients aged > 60 years, most of them already have preoperative bilateral lens opalescence. The worsening of the cataract in the year after vitrectomy is the most common surgery complication of ERM. The onset or continued worsening of postoperative cataracts may alter visual recovery and disrupt the assessment of visual function including retinal sensitivity microperimetry [25–27]. Furthermore, combined cataract surgery and vitrectomy for ERM is a commonly used technique that provides good functional results [28].

The main non-inclusion criteria are the presence of another pathology: age-related macular degeneration; retinal vein occlusion; diabetic retinopathy; glaucoma with macular visual field defect; or uveitis. Patients who underwent any recent eye injuries or eye surgeries (> 6 months) are also excluded. All the inclusion and non-inclusion criteria are in the Table 1.

**Table 1 Tab1:** Inclusion and non-inclusion criteria

Inclusion criteria	Non-inclusion criteria
✓ Adult patients (aged > 18 years), woman without childbearing potential or active contraception (intrauterine device, contraceptive pill, or contraceptive implant)	✓ Patient with other retinal pathologies such as age-related macular degeneration (“AMD”), retinal vein occlusion, diabetic retinopathy, glaucoma with macular visual field defect

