✓ Patients with an idiopathic symptomatic epimacular membrane; for patients with both eyes affected, the treated eye in the protocol will be the one that is most severely affected	✓ Patients with uveitis or a history of uveitis
✓ Pseudophakic patients with transparent posterior capsule or open capsule or lensed patients with age-related cataracts	✓ Patients with any recent eye injuries or eye surgeries (< 6 months)
✓ Patients with social security	✓ Patients participating in interventional clinical trial
✓ Patients able to understand and follow the trial instructions	✓ Pregnant or breastfeeding women
✓ Patients who have signed an informed consent	✓ Vulnerable people: persons deprived of liberty, under trusteeship, or under curatorship

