**Fig. 1 Fig1:**
[figure not shown]
Study diagram

On the day of the surgery (D-0), for phakic eyes with cataract, phacoemulsification is performed. For all patients, central and peripheral vitrectomy (25 gauge) and dissection of the ERM are performed. Membraneblue-Dual® is used to stain ILM for an exposure time of 1 min. Intraoperative pictures are then taken to see the possible spontaneous ILM peeling: if ILM remains, the patient is randomized in the operating room in the “no peeling” group or in the “active peeling” group. In the “active peeling” group, the ILM peeling is performed on at least two papillary diameters around the fovea, which corresponds to a “circle” of four papillary diameters.

At the end of the surgery, the retinal periphery is checked. The operation is filmed and the anonymous videos are centralized in Nantes to compare the appearance of microscotomas and grip areas of the ERM and ILM seen by video and photo. For about 30% of patients [29], the ILM is spontaneously peeled off. These patients are not randomized but they can be included, if they want it, in the ancillary study. This ancillary study has the same follow-up visits (at 1, 6, and 12 months) with the same examinations as the principal study.

A total of three follow-up visits are planned over a time span of 12 months postoperatively (at 1, 6, and 12 months). At each visit, the following are performed: VA on the ETDRS scale; near vision (Parinaud scale); SD-OCT; microscopic examination of the eye; microperimetry; fundus photography and postoperative “Patient discomfort” questionnaire; biomicroscopic examination of the anterior segment; retinal photography; and an assessment of adverse events (AE). The schedule of the trial is shown in Table 2. To avoid any bias, the follow-up visits are made by masked ophthalmologists and orthoptists who do not know if ILM was actively peeled off.

**Table 2 Tab2:** Study schedule

Actions	Inclusion visit D-90 and D-7	D0 (Surgery)	M1 (30days±7days starting D0)	M6 (6 months ± 15 days starting D0)	M12 (12 months ± 15 days starting D0) End of study
Patient information	X				
Informed consent	X				
History (medications taken…)	X				
Randomization		X			
Surgery		X			
ETDRS visual acuity score and near vision (Parinaud)	X		X	X	X
Evaluation of the appearance of the lens at the slit lamp	X				
Biomicroscopic examination of the anterior segment	X		X	X	X
Fundus	X		X	X	X
SD OCT	X		X	X	X
OCT/SLO: microperimetry	X		X	X	X
Retinal photography	X		X	X	X

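### Adding lens status to the primary model would gain a little precision at almost no cost; the planned model without it is valid and keeps its power.

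*Protocol article*

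**What the plan says.** The section on statistical methods {20a} defines the outcome: "The primary endpoint is the difference between the number of microscotomas measured before surgery and the number of microscotomas measured at 6 months". The arms are compared with a mixed linear regression whose stated adjustments are "the center will be considered as a random effect) and adjustment for the preoperative number of microscotomas". Under Sequence generation {16a}, center is the only stratification factor.

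Table 1 admits two kinds of eye: "Pseudophakic patients with transparent posterior capsule or open capsule or lensed patients with age-related cataracts". Microperimetry is first done at the visit headed "Inclusion visit D-90 and D-7" in Table 2. On the day of surgery, "for phakic eyes with cataract, phacoemulsification is performed" (Interventions description {11a}). Table 2 also schedules, at inclusion, "Evaluation of the appearance of the lens at the slit lamp".

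The section on eligibility criteria {10} comments on cataract and the measurement: "The onset or continued worsening of postoperative cataracts may alter visual recovery and disrupt the assessment of visual function including retinal sensitivity microperimetry".

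**The concern.** A phakic eye has its baseline count taken through a cataract and its 6-month count taken after the cataract is gone. A pseudophakic eye has no such change of lens. The same preoperative count can therefore reflect retinal loss in one eye and partly media opacity in the other, and a single baseline slope cannot represent both.

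What is at stake is precision. Lens status is fixed before randomization, is recorded anyway, and may carry information about what the baseline count means. With 53 per arm and half the eyes phakic (assumed), the 95% range for chance imbalance in lens status is about ±1.96 × √(0.25 × 2/53) = ±19 percentage points.

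**Working it through.** **Inputs from the protocol (Sample size {14}).** Planned means are 6 (SD 6) against 3 (SD 4.6), power is 80%, type I error is 5%, 100 patients are evaluable, and loss is at most 5%. The pilot baseline count is 2.5 (SD 3.1), from 11 patients. The test is taken as two-sided, since sidedness is not stated.

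**The plan's own figure.**
- Root-mean-square SD = √((6² + 4.6²)/2) = √28.58 = 5.346.
- n per arm = 2 × 28.58 × (1.960 + 0.842)² / 3² = 49.9, so 50 per arm and 100 in total.
- 100/0.95 = 105.3, so 106 randomized.
- Power at 50 per arm: SE = 5.346 × √(2/50) = 1.069; 3/1.069 − 1.960 = 0.846; power 80.1%.

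The stated size reproduces, and it takes no credit for covariate adjustment.

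**Where the cataract acts.** When the baseline count is a covariate, the treatment estimate for the change is algebraically the same as for the month-6 count. Over 20,000 simulated trials the largest difference between the two was 6 × 10⁻¹⁵. The month-6 count is taken after the cataract has been removed. The baseline artefact therefore does not pass directly into the comparison; it only weakens the baseline count as a predictor.

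**Size of that weakening.** Three quantities are assumed because the protocol gives none of them: the phakic share p (0.3 to 0.7), the extra baseline microscotomas due to cataract c (1 to 4), and the correlation ρ (0.3 to 0.7) between the artefact-free baseline count and the month-6 count. The total baseline SD is held at 3.1.
- Lens part of the baseline variance: c²p(1 − p). Remainder: vT = 3.1² − c²p(1 − p).
- Correlation the planned model can use: r = ρ√vT/3.1.
- Residual variance without lens status: 28.58 × (1 − r²). With it: 28.58 × (1 − ρ²).

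Example with p = 0.5, c = 2, ρ = 0.5:
- vT = 9.61 − 1 = 8.61 and r = 0.5 × 2.934/3.1 = 0.473.
- Variances are 22.18 without lens status and 21.44 with it, a fall of 3.4%.
- SE without: √(2 × 22.18/50) = 0.942; 3/0.942 − 1.960 = 1.225; power 89.0%.
- SE with: √(2 × 21.44/50) = 0.926; 3/0.926 − 1.960 = 1.280; power 90.0%.

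| p | c | ρ | Fall in residual variance | Power without lens status | Power with lens status |
|---|---|---|---|---|---|
| 0.5 | 1 | 0.3 | 0.3% | 83.6% | 83.7% |
| 0.5 | 2 | 0.5 | 3.4% | 89.0% | 90.0% |
| 0.5 | 3 | 0.5 | 7.2% | 87.7% | 90.0% |
| 0.5 | 2 | 0.7 | 9.1% | 96.3% | 97.6% |
| 0.5 | 4 | 0.3 | 4.0% | 82.2% | 83.7% |
| 0.5 | 4 | 0.7 | 28.6% | 91.3% | 97.6% |

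For c of 2 or less, the gain is at most 1.3 points anywhere in the grid. The lowest power without lens status in the grid is 82.2%.

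**Simulation check (p = 0.5, c = 2, ρ = 0.5, true effect 3).** Mean estimates were 3.007 without and 3.008 with lens status, so neither model is biased. Empirical SEs were 0.943 and 0.931, a gain of about 1.3%.

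**The case against.** The strongest reply is that nothing stated here is wrong. Under randomization, the planned model gives an unbiased comparison. Chance imbalance is possible for any covariate left out, and the standard error already allows for it. Further covariates are commonly left to an analysis plan. Most of this stands, and it is why the point is an improvement and not an error. What remains is that the article itself names the primary covariates, and lens status is not among them although it is collected.

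Three stronger readings are tempting, and the documents do not support them.

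- **A reader might infer that cataract removal contaminates the treatment effect because it enters the change score.** Adjustment for the preoperative count removes that route, as shown above.
- **A reader might infer that the protocol itself declares the baseline measurement unreliable.** The sentence that cataract "may alter visual recovery and disrupt the assessment of visual function including retinal sensitivity microperimetry" has postoperative cataract as its subject and serves as background to combined surgery. Extending it to preoperative cataract is optically reasonable, but it is an inference.
- **A reader might infer that power falls below 80%.** An illustrative simulation of the 29-point grid with a 10 dB cut, 106 eyes, 60% phakic (assumed) and mean cataract losses of 1.5, 3 and 5 dB gave SEs without lens status of 0.726, 0.791 and 0.873. At the planned difference of 3, these correspond to about 98.5%, 96.7% and 93.0% power. A figure in the sixties needs a true difference of about 2 (2.0/0.873 − 1.960 = 0.33, about 63%), which is not the planned effect. In a similar simulation, the 3 and 5 dB cases implied baseline counts in phakic eyes of about 10 and 16, far above the pilot's 2.5.

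**Conclusion.** The point holds as a minor one. Leaving lens status out of the primary model gives up some precision; it causes no bias and no shortfall against the planned 80% power. At a difference of 3 with 50 per arm, the gain from including it is about 0 to 2 power points in moderate scenarios. It reaches about 6 points (91.3% to 97.6%) only in the extreme case where cataract adds four microscotomas and the underlying baseline count strongly predicts month 6.

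These figures rest on assumed values of p, c and ρ, on a linear model with the pilot's baseline SD, and on lens status and combined surgery having no effect of their own on the month-6 count. If they do have one, the gain would be larger.

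**What to change.** Before unblinding, prespecify lens status at surgery (pseudophakic against phakic with combined phacoemulsification) as a fixed main effect:

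- in the primary model, beside center and the preoperative count;
- in the multiple-imputation model for the primary endpoint;
- in the models for change in mean retinal sensitivity and visual acuity.

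Keep the interaction of lens status with the centered preoperative count as a sensitivity analysis.

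The cost is one degree of freedom in each model and a sentence in the analysis plan. No new data are needed, since the lens is examined at inclusion and phacoemulsification is part of the study surgery. If cataract turns out not to matter, the loss is negligible: in a simulation with no cataract effect, adding both the main effect and the interaction raised the SE by about 0.7%.

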#### Outcomes {12}

The main endpoint is the difference between the number of microscotomas (sensitivity < 10 dB) found before surgery and the number of microscotomas found at 6 months (number in the range of 0–29).

The secondary endpoints are:
VA measured on the ETDRS scale and near vision (Parinaud) (at inclusion visit and 1, 6, and 12 months after surgery)Number and types of microscotomas by microperimetry (before and after surgery)Mean retinal sensitivity by microperimetry before and after surgery (at 1, 6, and 12 months)Patient visual discomfort questionnaire: symptoms and subjective improvement before and after surgery (at 1, 6, and 12 months)Incidence of changes of the retinal nerve fiber layer SD by OCT analysis (B scan and C scan) before and after surgerySinusoid (IS/OS) line disruption by OCT analysis (B scan and C scan) before and after surgeryMean retinal thickness by OCT analysis (B scan) before and after surgeryRetinal nerve fiber layer thickness by OCT analysis (B scan) before and after surgeryOuter segment photoreceptor thickness by OCT analysis (B scan) before and after surgeryRecurrence of ERM by OCT analysis (B scan and C Scan)Operative report and the video recording area of ERM and ILM gripping (study of the correlation with the microscotoma(s).

The endpoints of the ancillary studies are:
The main criterion: the difference between the number of microscotomas (sensitivity < 10 dB) found before surgery and the number of microscotomas found at 6 months (number in the range of 0–29).VA measured on the ETDRS scale and near vision (Parinaud) (at inclusion visit and 1, 6, and 12 months after surgery)Number and types of microscotomas by microperimetry (before and after surgery)Mean retinal sensitivity by microperimetry before and after surgery (at 1, 6, and 12 months)Patient visual discomfort questionnaire: symptoms and subjective improvement before and after surgery (at 1, 6, and 12 months)Incidence of changes of the retinal nerve fiber layer SD by OCT analysis (B scan and C scan) before and after surgerySinusoid (IS/OS) line disruption by OCT analysis (B scan and C scan) before and after surgeryMean retinal thickness by OCT analysis (B scan) before and after surgeryRetinal nerve fiber layer thickness by OCT analysis (B scan) before and after surgeryOuter segment photoreceptor thickness by OCT analysis (B scan) before and after surgeryRecurrence of ERM by OCT analysis (B scan and C scan)

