#### Sample size {14}

A retrospective study conducted in the Department of Ophthalmology of the University Hospital of Nantes in 2013 [23] showed that of 11 patients who received active peeling, the number of microscotomas was 2.5 ± 3.1 preoperatively and 6.5 ± 7.3 at 1 month.

Based on the number of microscotomas found in the active peeling group in our retrospective study, with 80% power and a type I error of 5%, 100 patients are needed to highlight a halving of the number of microscotomas in the non-peeling group relative to the active peeling group (i.e. 6 ± 6 microscotomas average peeling in the active group compared to 3 ± 4.6 in the non-peeling group).

Usually, only very few patients do not attend their 6-month visit. However, the occurrence of EIGs (endophthalmitis, retinal detachment) may prevent the determination of the number of microscotomas at 6 months by microperimetry. Assuming that at most 5% of patients will be affected, 106 patients will be randomized, or 53 patients per group.

As all the patients with spontaneous peeling during surgery will not be randomized, > 106 have to be enrolled. The estimated number of spontaneous peeling was initially 30% [23], so the number of patients enrolled were thought to be 156. During the study, we noted that spontaneous peeling occurred in 50.2% of cases and so the number of patients to enroll in the study has been revised to 222 patients (amendment to the protocol in December 2017).

The ability of the six centers to recruit is estimated to be 120 patients per year (30 patients per center), given that the primitive ERM is a common disease.

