### Data collection and management

#### Plans for assessment and collections of outcomes: description of the parameters for evaluating efficacy {18a}

Here are detailed the parameters to assess effectiveness:

First, the microperimetry is a non-invasive test that allows a real-time, qualitative, and quantitative assessment of visual function. Microperimetry is introduced in routine clinical diagnostic procedure which, with extreme precision, defines the retinal attachment point and the threshold of differential sensitivity of the retina. Retinal sensitivity is better within 3° around the fixing point, with a mean foveal threshold of 20 dB, and a 0.275 dB mean decrement for each 10°. Scotomas are defined as absolute (if the patient does not perceive the maximum stimulation, the sensitivity is 0 dB) or relative (reduction of retinal sensitivity compared to normal values is < 10 dB). Assessing retinal function with this tool provides valuable clinical and pathophysiological information. These abnormalities could explain the hitherto non-assessable visual discomfort by conventional methods reported by some patients undergoing epiretinal membrane or macular hole surgery.

For all patients and to standardize the measurement, we use the “Ivana” protocol directed by the ophthalmology service of Lariboisière: a fixation target consisting of a red cross 2° in diameter, a white background monochromatic 4 asb, stimulus size Goldmann II with a projection time of 200 ms and a grid of 29 measurement points in the central 9° (centered on the fovea) with a 4–2-1 “double staircase” threshold strategy. Automatic “eye-tracking” will record eye movements throughout the exam. In addition, we will conduct topographies of the macular area in spectral OCT/SLO combined with microperimetry (OPKO/OTI, Miami, FL, USA).

Second, the scale of evaluation of the ETDRS VA will be performed by a masked orthoptist so as not to influence the patient’s response.

Third, a “Patient discomfort” questionnaire made by the ophthalmologist team will be given to the patient to evaluate their symptoms before and after the surgery.

Fourth, the SD-OCT will allow a precise anatomical pre- and postoperative analysis of the macula. The projected sequences include:
RASTER (B scan): 1024 A scans; 25 sections (nine frames) spaced by 240 μm, covering an area of 20° × 20°FRONTAL acquisition (C scan): 512 A scans; 193 sections (16 frames) spaced by 30 μm, covering an area of 20° × 20°.

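### Symptom frequencies are compared by center-stratified chi-square tests that leave out the preoperative questionnaire, which costs precision in the randomized comparison and leaves baseline differences uncontrolled in the ancillary one

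*Protocol article*

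**What the plan says.** Statistical methods {20a} of the protocol article covers "The comparison between the two groups in the frequency of symptoms (blurred vision, metamorphopsia, relative scotoma, diplopia and micropsia"), together with OCT abnormalities and recurrence at 12 months. All of these "are analyzed by Chi-square tests stratified on the center". No baseline term or change measure is named for the symptoms.

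Elsewhere the article treats the symptoms as a before-and-after outcome:

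- Outcomes {12} lists the endpoint as "Patient visual discomfort questionnaire: symptoms and subjective improvement before and after surgery (at 1, 6, and 12 months").
- Plans for assessment {18a} says that the questionnaire "will be given to the patient to evaluate their symptoms before and after the surgery". Table 2 marks it at the inclusion visit and at months 1, 6 and 12.
- In the same section {20a}, the primary endpoint has "adjustment for the preoperative number of microscotomas", and visual acuity and mean retinal sensitivity are compared as changes.
- Eligibility criteria {10} states: "The study population concerns only patients with symptomatic idiopathic ERM, responsible for symptoms such as decreased VA and metamorphopsia".

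Methods for additional analyses {20b} applies a stratified chi-square test to the comparison of the non-randomized spontaneous-peeling patients with the active-peeling arm. It does not name the stratum, which is taken here to be center, as in the main study.

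**The concern.** A symptom present after surgery can be one that the patient already had or one that is new. The planned test pools the two and makes no use of the preoperative answer, although that answer is on file. If preoperative presence predicts presence at follow-up, ignoring it leaves explainable variation in the comparison. It also lets a chance difference between the arms at baseline carry through to the result.

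The questionnaire is the only patient-reported instrument listed; acuity and microperimetry are performance tests. Visual discomfort is the clinical reason given for counting microscotomas. The end of the Discussion links a possible contraindication of peeling to microscotomas and patient discomfort together.

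The ancillary comparison is more exposed. Whether the ILM comes away spontaneously is not assigned at random, so nothing in the design balances preoperative symptoms between those patients and the active-peeling arm.

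**Working it through.** **1. Arm size, from the plan's own figure.** Sample size {14} states "with 80% power and a type I error of 5%, 100 patients are needed to highlight a halving of the number of microscotomas", with 6 ± 6 against 3 ± 4.6. The common variance is (6² + 4.6²)/2 = 28.58, so the SD is 5.346. With a two-sided 5% level (assumed), n per arm = 2 × (1.960 + 0.842)² × 28.58 / 3² = 49.9, or 50 per arm and 100 in total. Allowing for 5% loss, 100/0.95 = 105.3, or 106 randomized and 53 per arm. The stated figures reproduce. The article gives no power figure for symptoms; this step only fixes the arm size.

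**2. Chance imbalance at baseline.** The 95% range of the difference between arms is ±1.96 × √(2p(1−p)/53).
- p = 0.5: ±0.190, about 19 percentage points.
- p = 0.7: ±0.174, about 17 percentage points.

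Suppose a symptom persists in 50% of those who had it and arises in 10% of those who did not. A 19-point imbalance then moves the follow-up difference by 0.19 × (0.50 − 0.10) = 0.076, or 7.6 points. These rates are assumed.

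**3. Power with fixed follow-up frequencies.** Assumptions: 106 patients, six centers, 1:1 allocation within center, symptom frequency at follow-up 25% (no peeling) against 50% (active peeling), 4000 simulated trials per row. As a check, the closed-form power for 25% against 50% at 53 per arm is 76.5%, in line with the planned test below.

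| Baseline prevalence | Odds ratio, baseline to follow-up | Center only (planned) | Center × baseline | Change | Baseline only |
|---|---|---|---|---|---|
| 50% | 1 | 78.1% | 75.0% | −3.1 | 77.4% |
| 50% | 3 | 78.1% | 77.7% | −0.4 | 79.6% |
| 50% | 8 | 77.6% | 83.1% | +5.5 | 85.0% |
| 50% | 20 | 77.1% | 89.1% | +12.0 | 91.0% |
| 70% | 1 | 76.2% | 73.5% | −2.7 | 75.9% |
| 70% | 3 | 77.4% | 76.2% | −1.2 | 78.3% |
| 70% | 8 | 76.6% | 79.8% | +3.2 | 81.5% |
| 70% | 20 | 78.1% | 83.8% | +5.7 | 85.1% |

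The change column compares the planned test with center × baseline strata. Stratifying on baseline alone gains at most 91.0 − 77.1 = 13.9 points, but drops the randomization stratum.

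**4. Power with a fixed conditional odds ratio of 3, 50 per arm.** The pairs are follow-up rates with and without the symptom at baseline. The first power figure is the planned center-stratified test, the second is center × baseline strata. Ranges come from repeated sets of simulations.
- Strong association: 70% baseline, 50%/10% (odds ratio 9): 59–61% to 65–66%.
- Strong association: 60% baseline, 60%/10% (odds ratio 13.5): 48–51% to 59–60%.
- Strong association: 50% baseline, 70%/10% (odds ratio 21): 37–38% to 50–52%, a gain of 13 to 15 points.
- Weak association, 40%/20% (odds ratio 2.7): 76% to 74% at 70% baseline; 73% to 71% at 50% baseline.
- Symptom nearly universal before surgery (95%) or rare (10%), 50%/10%: 72% to 72% and 49% to 49%.

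**5. Type I error.** Under the null (2000 trials per scenario of step 3) all three tests reject in 3.6% to 5.4% of trials.

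**6. Ancillary comparison.** Steps 2 to 5 rely on random allocation and do not carry over. Without it, a difference in preoperative symptoms can be systematic, and a test stratified only on center attributes its consequences to the type of peeling.

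**The case against.** The strongest reply is that this is a preference about efficiency. Randomization is 1:1 and stratified by center, and the planned test matches that. Chance baseline imbalance is already part of its 5% error rate, and adjusting the primary endpoint does not oblige the same for every binary secondary one. This stands for the randomized comparison. A reader might infer from the missing baseline term that the result would be biased or the test invalid; the design and step 5 do not support that.

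Second, the gain is not assured. The article gives no symptom rates, and large gains appear only under strong association. A reader might infer from the symptomatic population that most follow-up symptoms are persisting ones. Of the five symptoms compared, the eligibility text names only metamorphopsia, so that inference is undocumented for relative scotoma, diplopia and micropsia. This also stands, and is why the range is shown with its negative end.

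Third, a condensed article leaves much to an analysis plan. That holds for the main visit, the coding of symptom frequency and the effect estimate; a stratified chi-square test does not preclude a common odds ratio. None of these is counted here. It does not fully answer the point, because the article names the test and its stratum, and a plan that followed it as written would leave baseline out.

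Finally, symptoms are a secondary endpoint, and the Abstract and Background state the contraindication on microscotomas alone.

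**Conclusion.** The concern holds in limited form. The article fixes a symptom analysis that sets aside a preoperative measurement it collects, builds into the endpoint definition, and uses in the corresponding way for the primary endpoint. In the randomized comparison this means lost precision and exposure to chance imbalance of about ±17 to ±19 points in a baseline symptom (prevalence 70% or 50%, 53 per arm), with no bias and type I error of about 5%. The power effect of using baseline runs from about -3 points (unrelated or weakly related) to about +14 points (strongly related), all under assumed rates. In the ancillary comparison the weakness is one of confounding, and its size cannot be derived from the documents. Overall this is a worthwhile, nearly free improvement to a secondary analysis and does not threaten the primary result.

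**What to change.** For each symptom, add its preoperative presence to the analysis and keep center. Two suitable forms are logistic regression on arm, baseline symptom and center, or a Mantel-Haenszel test stratified on center and baseline symptom. Stratifying on baseline alone is not enough, because it drops the randomization stratum.

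Do the same in the ancillary comparison of spontaneous with active peeling. There it controls one known baseline difference but does not replace randomization.

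The cost is wording only; the data are already collected. Six centers by two baseline levels make 12 strata, or about 106/12 = 8.8 randomized patients each, so strata will be thin and a logistic model may be unstable for a rare symptom. The plan should state in advance what is done then. Where baseline turns out to be unrelated to follow-up, the finer stratification costs about 3 points of power.
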